**Secondary Outcomes:**

**Muscular Strength:** Leg press and chest press strength will be assessed using a 1-repetition maximum testing protocol. Following a standardized warm-up, participants will be asked to complete two exercise-specific warm-up attempts at 5-6 repetitions with ~50% estimated 1RM. Participants will complete another warm-up attempt with 3 repetitions at ~80% 1RM. Participants will then be asked to complete a maximal attempt of 1 repetition at the maximal load they can lift. A 1RM value will be recorded when participants can no longer lift the weight with safe technique. Handgrip strength will be assessed via handgrip dynamometry (Jamar Plus+; Sammons Preston, Rolyon, Bolingbrook, IL) due to the association of low grip strength with functional limitations, reduced quality of life, and mortality in aging.^2,77^

**Anthropometric Battery.** *Body weight* will also be measured to the nearest 0.1 kilogram using a calibrated and certified balance beam scale. *Height* without shoes will be measured to the nearest 0.1 centimeter using a stadiometer. *BMI* will be calculated using the body mass and height values.

***Physical Function: Short Physical Performance Battery Protocol (sPPB)*** The sPPB will be used to assess lower body physical function, comprising of assessments of balance (tandem and semi tandem), gait speed (4-meter walk test in m/s), and chair stand (5 times repeated chair stand). The sPPB is scored by summing the scores of each test, with lower scores indicating worse functioning.^98^ Self-reported physical activity will be obtained via the International Physical Activity Questionnaire, at baseline, follow-up and bi-weekly throughout the intervention to understand physical activity achieved outside the intervention.^99^

**Health-Related Quality of Life (HRQOL).** Cancer-specific HRQOL indices will be measured using the European Organization for Research and Treatment of Cancer QoL Questionnaire Core 30 (EORTC-QLQ-C30). Sarcopenia-related HRQOL will be assessed using a sarcopenia-specific questionnaire (SarQoL).^100^

**Blood Biomarkers:** Venous blood samples will be obtained into 10 mL vacutainer tubes using a 21-gauge needle inserted into the median cubital vein as described in our laboratory’s standard operating procedure [See Blood Draw SOP]. Blood samples will be stored at room temperature for 10 min and then centrifuged. Serum will be removed and frozen at -80C for later analysis. Total plasma concentrations of inflammatory mediators will be determined using quantitative sandwich ELISA kits provided by R&D Systems, Inc. (Minneapolis, MN). TNF-α (Cat. HSTA00D; sensitivity = 0.19ρg/mL), IL-6 (Cat. HS600B; sensitivity = 0.11ρg/mL) and CRP (Cat. DCRP00; sensitivity 0.022ng/mL) will be measured in all plasma samples. These markers have been linked to disease progression and muscle loss in cancer [3, 46-49].

*Banking for future analysis—*blood will be banked for later assessment of the correlation between genetics/genomics (DNA) or transcription (RNA) and muscle function as well as the levels of biomarkers related to inflammation and cancer progression.

**Skeletal Muscle Mass Regulation, Inflammation, and Mitochondrial Health:** Percutaneous muscle biopsies will be obtained from the middle portion of the vastus lateralis muscle of the dominant leg (midpoint between the patella and the greater trochanter of the femur) at a depth between 1 and 2 cm after subcutaneous administration of the local anesthetic, lidocaine (1 mL of 1% lidocaine) as previously performed by our group [61-66] and as described in our laboratory’s standard operating procedure [See Micro-Biopsy SOP]. After removal, adipose tissue will be trimmed from the muscle specimens and will be immediately snap frozen in liquid nitrogen (LN_2_) and stored at −80̊C for later analysis or place in 2.5% glutaraldehyde for electron microscopy. Protein will be extracted from frozen skeletal muscle biopsies and total protein content will be measured by the standard Bradford protein assay. Intramuscular markers of mitochondrial dynamics (PGC-1a, TFAM, Drp-1, Fis-1, MFN-1, MFN-2, Opa-1, BNIP3, parkin, LC3, P62, cytochrome C), content (complex I-V content, citrate synthase activity, VDAC) will be assessed. Alterations in these markers of mitochondrial quality control have been associated with muscle atrophy and sarcopenia [50-53]. Additionally, we will use electron microscopy to assess skeletal muscle mitochondrial density, morphology, and ultrastructure to further characterize skeletal muscle mitochondrial quality. Intramuscular markers of skeletal muscle anabolism (Akt, mTORC1, p70s6k) and catabolism (ubiquitin, myostatin, MuRF1/Atrogin1) will be assessed [26, 47, 54]. Skeletal muscle mass is tightly regulated by the balance between these anabolic and catabolic pathways [55-60] While not an exhaustive list, these markers are well established regulators of muscle mass, inflammation, and mitochondrial health.

*Banking for future analysis*—muscle will be banked for later assessment of protein signaling, gene expression, and other morphometric outcomes. Total protein, DNA, and RNA will be isolated according to standard procedures and then stored at -80°C.

**Statistical Analyses:** For this feasibility study, we hypothesize that we will be able to recruit (within a 12-month window) 40 cancer survivors, retain ≥75% of the sample, and have ≥75% adherence to the intervention.^101^ In line with NIH guidelines on pilot studies, data obtained from these tests will be critical to optimize the intervention procedures and inform the design of a future RCT.^88^ **Further, the NIH reinforces that the “goal of pilot studies is to assess feasibility/acceptability of an approach to be used in a larger scale study”**^89^ Rather, our **sample size** is based on “practical considerations regarding participant flow, budgetary constraints, and the number of participants needed to reasonably evaluate feasibility goals.”^89,102^ To evaluate estimates of effectiveness for a larger RCT, we will test for differences in change in mean concentrations of muscle strength, body composition, physical function, quality of life, biomarkers (IL-6, TNFα, CRP) and mitochondrial health/muscle cell signaling among the groups using analyses of variance. We will calculate Cohen’s d by dividing the difference in group means (control versus supplement groups) by the pooled standard deviation. We will test for relations between 1) baseline levels of fatigue and inflammatory biomarkers and 2) changes in biomarkers and changes in fatigue using Pearson or Spearman’s correlations

**Timeline:** [name] has almost a decade of experience in executing exercise trials with cancer patients. We have an established infrastructure for recruiting individuals with cancer, testing our outcomes, and delivering interventions. Developing our database, training personnel, trial registration and submission of protocol paper for publication, will occur in the first 3 months of the grant. Participant recruitment will begin in month 4 of year one. Specifically, we will aim to conduct the intervention in 5 waves of 8-10 individuals in each wave. We anticipate identifying 4-5 eligible and interested individuals per month, allowing us to achieve our target or 8-10 individuals per wave across the study timeline.

Recruitment for subsequent waves will be ongoing during intervention delivery of preceding waves (i.e., recruitment for wave 2 will be ongoing while wave 1 is completing the intervention). Data Collection will begin in Months 4/5 of year one and continue until month 10 of year two. The remaining of year two will be dedicated to analyses, manuscript preparation and presentation/publications.

|  | **Y1** | | | | **Y2** | | | |
| --- | --- | --- | --- | --- | --- | --- | --- | --- |
|  | **Q1** | **Q2** | **Q3** | **Q4** | **Q1** | **Q2** | **Q3** | **Q4** |
| **Development** |  |  |  |  |  |  |  |  |
| Preregister trial on clinicaltrials.gov | x |  |  |  |  |  |  |  |
| Submit Protocol Paper for Publication | x |  |  |  |  |  |  |  |
| Finalize Protocols | x |  |  |  |  |  |  |  |
| IRB Approval | x |  |  |  |  |  |  |  |
| Hire/Train research assistants | x |  |  |  |  |  |  |  |
| **Recruitment/Intervention** |  |  |  |  |  |  |  |  |
| Recruitment |  | x | x | x | x | x |  |  |
| Intervention Delivery |  | W1 | W2 | W3 | W4 | W5 |  |  |
| Assessments |  | x | x | x | x | x |  |  |
| Post Testing |  |  | x | x | x | x | x |  |
| **Data Analysis/Publication** |  |  |  |  |  |  |  |  |
| Data cleaning and analysis |  |  |  |  |  |  | x | x |
| Report Clinical Trial Results on clinicaltrials.gov |  |  |  |  |  |  |  | x |
| Present/Publish Results |  |  |  |  |  |  |  |  |

Table 1. Project Timeline

Participants recruited and enrolled in intervention in 5 waves (W1, W2 etc.) of 8-10 participants. Quarterly timepoints are estimates.

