**Principal Investigator Name: [name]**

**A. SPECIFIC AIMS**

We seek to conduct a pilot RCT, examining the effects of a 10-week multimodal resistance exercise and creatine intervention (EXSUPP) (n=20) relative to resistance exercise and creatine placebo (EXPLA) (n=20) in sarcopenic individuals who have previously been treated for colorectal cancer. **Our overarching objectives are** to **1)** determine the feasibility and acceptability of the EXSUPP intervention with **creatine monohydrate supplementation** (0.10 g/kg/day) and **2)** understand the intervention characteristics that can be used to inform the design of a future large RCT. **Our RCT is *significant* because** it will establish the feasibility and acceptability of combining creatine monohydrate with resistance exercise training in the management of sarcopenia in individuals with colorectal cancer, providing preliminary support for the integration of effective lifestyle interventions in the management of colorectal cancer care. This pilot RCT will provide important information for the design of a future large-scale RCT R01 submission. To test our hypothesis and achieve the application objectives, we propose the following ***Specific Aims*:**

**Primary Aims: 1(a) To explore the feasibility and acceptability of a 10-week RCT comparing EXSUPP to EXPLA in individuals who are sarcopenic after colorectal cancer treatment.** This aim will be accomplished by assessing accrual, retention, adherence, and adverse events, **and 1(b) to quantify (mean change scores and precision estimates) and compare between-arm differences in muscular strength,** the primary variable used to diagnose sarcopenia.^2^ We hypothesize that we will be able to recruit (within a 12-month window) 40 colorectal cancer survivors, retain ≥75% of the sample, and achieve ≥75% adherence to the resistance exercise intervention and ≥75% adherence to creatine/creatine placebo supplementation, with no adverse events experienced throughout the intervention. For aim 1(b), we hypothesize that the EXSUPP arm will experience a more favorable muscle strength response than the EXPLA arm following the intervention. The trial will be considered a success if feasibility outcomes are achieved, and the hypothesized directionality of the EXSUPP intervention effects on muscular strength is observed.

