**Aim 2. To obtain mean change scores and precision estimates and compare between-arm differences in secondary outcomes:** (a) body composition (whole-body and appendicular lean mass, whole-body fat mass and bone mineral content and density) (b) physical function, and (c) health-related quality of life measures.

**Exploratory Aim:** **Explore muscle molecular-level adaptations, i.e., mitochondrial health and protein turnover, in response to the interventions.** Cancer treatments have negative consequences on muscle cell signaling, mitochondrial health, and inflammation, and we will examine how these respond to exercise.

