**Supplementation.** Participants in the creatine group will receive creatine monohydrate supplementation (Optimum Nutrition, USA) at a dose of 0.10g/kg/day. This dose has been used in RCT’s involving older adults and individuals with cancer.^82,83^ Participants in the placebo group will receive a creatine placebo supplement (corn-starch maltodextrin; *Bulk Supplements, Nevada, USA*) in the same dose and schedule as EXSUPP. Participants will be instructed to consume 0.05g/kg/day of their supplement with food in the morning and 0.05g/kg/day with food in the afternoon or evening. Both groups will have similar flavor supplements to mask taste and solubility. **Supplement Adherence:** Supplements will be provided using smart-pill bottles (Pillsy, Inc; Seattle, WA), that will be used to automatically track number of times bottles are opened and return estimates of compliance to supplementation. The smart-pill bottles are accompanied by an app, which tracks when the bottle is opened, tracks remaining doses and has reminders/alarms for missed doses. For adherence, it is assumed that opening the bottle cap signifies consumption of a daily dose. As such, adherence to supplementation will be quantified as number of daily doses consumed across the intervention, relative to what could have been consumed. The reliability of smart pill bottles to track medication adherence has been published recently and has been demonstrated to improve adherence in cancer.^95-97^

**Study Outcomes:** Study outcomes will be assessed within 1 week of initiation and completion of the intervention.

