**E. PROTECTION OF HUMAN SUBJECTS**

1.  TARGET POPULATION:

Individuals ≥12 months post treatment for colorectal cancer (n=40), who are over the age of 18 and meet the criteria for sarcopenia will be eligible to participate. About 90% of those who get colorectal cancer are older than 40, and in the rare instances of a colorectal cancer diagnosis under the age of 18, cancer risk and survival is not as strongly linked to lifestyle factors such as physical activity. In addition, treatment strategies and subsequent side effects also differ between child and adult survivors of cancer. Furthermore, the proposed resistance exercise protocols are designed for adults, and may not be appropriate for children. There will be no upper limit placed on age. About a third of the individuals who are diagnosed with colorectal cancer are 65 years or older. Therefore, we anticipate the majority of our subject population will be mid-life and older adults. The investigative team has expertise working with adults and older adults. Dr’s [name] and [name] have experience conducting interventions with older adults living with and without cancer, ranging from 18-85. In addition, as medical oncologist Dr.’s [name] treats patients ranging from 18 years old to end of life. Depending on the age distribution of participants who enroll, age may be considered as a covariate in analyses as needed.

Twelve months post treatment or greater was chosen to allow full recovery from the acute side effects of treatment that might influence exercise tolerance. Specifically, the SARC-F questionnaire will be used to screen individuals. The SARC-F is a self-administered questionnaire used to determine the level of difficulty experienced in 5 components comprising the strength, assistance in walking, rising from a chair, climbing stairs, and history of falls; a score of 0–2 points is assigned for each item. The total score ranges from 0 to 10, with scores of ≥4 points indicating the risk of sarcopenia. Participants will be excluded if they 1) are receiving active treatment for their cancer; 2) have a any contraindication to exercise participation; 3) have been participating in structured resistance exercise 2 or more times per week for the past 6 months; 4) are currently taking supplements containing creatine for 4 weeks prior to the start of the RCT, or 5) are receiving medications that might alter body composition (metformin, corticosteroids etc.).

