Participants will also be offered a $50 incentive to receive an optional muscle biopsy at each assessment timepoint. Therefore, the total rumination for participants who complete both timepoints and receive a muscle biopsy at each timepoint is $200.

9. WITHDRAWAL:

Participants will be informed that their participation in this research is completely voluntary and made to understand that they are allowed to withdraw from the study from any time, without justification. All participants will be asked to inform a member of the study team of their decision and reason to withdrawal but will be informed that their withdrawal will not affect their relationship or any future opportunities to participate in research with the university. No additional information will be collected after an individual withdraws, through data collected up until the point of withdrawal will be used in analyses and interpretation of results.

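### Comparing strength and the other continuous outcomes by unadjusted ANOVA on change uses the baseline values inefficiently; adding each outcome's baseline as a covariate is a small and nearly free improvement

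*Protocol*

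**What the plan says.** The protocol's Section D, Statistical Analyses, fixes the between-arm comparison: "we will test for differences in change in mean concentrations of muscle strength, body composition, physical function, quality of life", then inflammatory biomarkers and mitochondrial and muscle-signalling markers, "among the groups using analyses of variance". The baseline value of the outcome is not mentioned as a covariate. The only covariate named anywhere is age, in Section E, item 1, and only as an option: "age may be considered as a covariate in analyses as needed".

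Baseline values will be available for these outcomes, since "Study outcomes will be assessed within 1 week of initiation and completion of the intervention" (Section D).

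Section A sets the purpose. Aim 1(b) is to "quantify (mean change scores and precision estimates) and compare between-arm differences in muscular strength", and Aim 2 is "To obtain mean change scores and precision estimates and compare between-arm differences in secondary outcomes". The success rule combines the feasibility targets with the requirement that "the hypothesized directionality of the EXSUPP intervention effects on muscular strength is observed".

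Section E, item 1, plans 20 participants per arm and expects retention of about 75%.

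**The concern.** A change score subtracts the whole baseline value, which amounts to assuming that follow-up rises one-for-one with baseline. When the true slope is below 1, part of what is subtracted is noise. Participants who start high then tend to show smaller gains through regression to the mean, and an arm that happens to start higher is put at a disadvantage. Analysis of covariance (ANCOVA) estimates the slope from the data and removes that conditional shift.

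What is at stake is the precision of the strength and secondary estimates that the pilot is meant to hand on, and the sign of the strength difference, which is part of the success rule. Reading the text as a repeated-measures ANOVA does not change this. With one pre and one post visit, the group-by-time test is the same test as ANOVA on change.

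**Working it through.** **Inputs**
- From the protocol: 20 per arm; about 75% retention; one pre and one post assessment.
- Not in the protocol, so assumed: the baseline–follow-up correlation r (shown from 0.3 to 0.95); equal SDs at both visits (set to 1). All results are in units of the outcome SD.

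**Completers.** 20 × 0.75 = 15 per arm.

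**Variance of the estimated arm difference, n = 15 per arm**
- Change score: 2(1 − r) × 2/n, with 28 df.
- ANCOVA: (1 − r²) × 2/n × [1 + 1/(2n − 4)], with 27 df. The bracket is the small-sample cost of estimating the slope: 1 + 1/26 = 1.038.

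Example at r = 0.5:
- Change: 1.0 × 2/15 = 0.1333, SE 0.365.
- ANCOVA: 0.75 × 2/15 × 1.038 = 0.1038, SE 0.322.
- Multiplying by the t quantiles gives 95% CI half-widths of 0.748 and 0.661, a reduction of 11.6%.

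| r | SE change | SE ANCOVA | Half-width change | Half-width ANCOVA | CI narrower by | Change-score n per arm with the same variance as ANCOVA at 15 |
|---|---|---|---|---|---|---|
| 0.3 | 0.432 | 0.355 | 0.885 | 0.728 | 17.7% | 22.2 |
| 0.5 | 0.365 | 0.322 | 0.748 | 0.661 | 11.6% | 19.3 |
| 0.7 | 0.283 | 0.266 | 0.579 | 0.545 | 5.9% | 17.0 |
| 0.8 | 0.231 | 0.223 | 0.473 | 0.458 | 3.2% | 16.0 |
| 0.9 | 0.163 | 0.162 | 0.335 | 0.333 | 0.5% | 15.2 |
| 0.95 | 0.115 | 0.116 | 0.237 | 0.238 | −0.8% | 14.8 |

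**Shift given the imbalance that occurs.** The chance baseline difference D has SD √(2/15) = 0.365. For a given D the change-score estimate moves by −(1 − r)D, that is, against the arm that starts higher. At D = 0.365 the shift is 0.18 SD at r = 0.5, 0.11 at 0.7, 0.07 at 0.8 and 0.04 at 0.9.

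**The two effects are one quantity.** Before the small-sample cost, the variance difference is [2(1 − r) − (1 − r²)] × 2/n = (1 − r)² × 2/n. This is the square of (1 − r) × 0.365. At r = 0.5: 0.1333 − 0.1000 = 0.0333 = 0.183².

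**Simulation check (20,000 trials per r).** Variance ratios of ANCOVA to change were 0.78, 0.89 and 0.99 at r = 0.5, 0.7 and 0.9, against 0.78, 0.88 and 0.99 by formula. For D between 0.30 and 0.45 the change-score shift was −0.184, −0.111 and −0.040; the ANCOVA shift was about zero.

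**Effect on the direction criterion.** For an assumed true effect of 0.3 SD, the chance of observing the right sign goes from 79.4% to 82.4% at r = 0.5, from 85.6% to 87.1% at 0.7, and from 96.7% to 96.8% at 0.9.

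**The case against.** The strongest defence is that ANOVA on change is a legitimate method that matches the aims, which name mean change as the quantity to report. Feasibility is primary, and the sample size rests on it. The gain also depends on a correlation that nobody has stated. Repeated maximal-strength or body-composition measurements could plausibly correlate at 0.9 or above, where the gain disappears. Unequal SDs can remove it sooner. If the follow-up SD were 1.2 times the baseline SD (an assumption), then at r = 0.8 the variance ratio would be 1.44 × 0.36 / (1 + 1.44 − 2 × 0.8 × 1.2) = 0.518/0.520 = 0.997, before any small-sample cost. All of this stands, and it limits the size of the point. It does not remove it: the method is stated, the baseline values are collected, and using them better costs almost nothing.

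A reader might infer more than the protocol supports:
- **That baseline data are thrown away, or that the estimate is biased.** Neither is so. A change score uses each completer's baseline, with slope 1, and is unbiased over randomisation. The shift is conditional on the imbalance that happens to occur.
- **That the imbalance shift is a second harm on top of lost precision.** It is the same variability seen another way, and the change-score interval already contains it.
- **That the gain is (1 + r)/2 in variance, worth 11–33% more participants.** That is the large-sample figure for r of 0.8 down to 0.5. With 15 per arm the equivalent is 16.0 to 19.3 per arm, or 7–29%.
- **That the method contradicts the withdrawal statement** in Section E, item 9, that "data collected up until the point of withdrawal will be used in analyses". Data up to withdrawal still feed the feasibility outcomes, and a plain ANCOVA also excludes anyone without a follow-up value.

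The optional age covariate is a separate matter. The scale for the biomarkers and the interval and SD for Cohen's d are details that a statistical analysis plan may settle.

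**Conclusion.** The point holds as a minor efficiency improvement to a stated method. Under equal visit SDs and 15 completers per arm, baseline adjustment narrows the 95% CI by about 12% at r = 0.5, 6% at 0.7 and 3% at 0.8. It gives essentially nothing at 0.9 and costs just under 1% at 0.95. Outcomes with lower test–retest correlation gain most. The effect on the direction criterion is at most a few percentage points under the assumed 0.3 SD effect.

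The planned analysis is not invalid, and nothing here threatens the feasibility conclusions. The change is worth making because the sign of the strength difference counts towards success and because these estimates are meant to inform a larger trial.

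**What to change.** In Section D, Statistical Analyses, replace the ANOVA on change with a linear regression of the 10-week value on arm and the baseline value of the same outcome. Regressing the change on the same two terms gives an identical arm effect, so either wording will do. Report the adjusted between-arm mean difference with its 95% CI for each outcome, which supplies the precision that Aims 1(b) and 2 promise. Unadjusted mean change per arm can still be shown descriptively. State that the direction criterion for strength is read from the adjusted difference.

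The cost is a change of wording and one degree of freedom (27 instead of 28 with 15 per arm). No visit or measurement changes. The downside is little or no gain, and possibly a very small loss, for outcomes with very high test–retest correlation.

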A convenience sample (n=40) will be recruited to determine the feasibility of the intervention. The rationale for this is in line with recommendations from Julious et al (2005) that justify an n=12 as a minimum based on feasibility, gains in precision surrounding the mean and variance, and ability to estimate parameters for future studies.^103^ Consequently, given that our study has two arms, and in line with other exercise oncology trials in anticipation of an ~75% retention rate, we aim to recruit 20 individuals per arm to participate in full study activities.

2. RECRUITMENT PLANS:

Recruitment will occur in collaboration with two healthcare partners (PRISMA Health and South Carolina Oncology Associates, [SCOA]). SCOA is a medical and radiation oncology practice affiliated with an ACOS-approved Integrated Network Cancer Program in central South Carolina. PRISMA Health-Midlands provides multidisciplinary cancer care in Columbia that is a part of the larger PRISMA Health system. Participants will be recruited by 1) use of cancer registry data bases at local health care system’s cancer programs to prepare personalized invitations, and 2) outreach with various cancer support groups and organizations. We will also request a partial HIPAA waiver from the cancer clinics to recruit from patient lists of contact information. Specifically, the covered entity (Prisma), will provide us with a secure list of individuals previously treated for colorectal cancer, and their PHI. This is one of our strongest methods of recruitment and are currently using it in several ongoing studies. From these lists, we will send an initial introductory letter to eligible patients from their oncology provider with information about the study. There will be a number to call if they do not wish to be contacted by study personnel. After a wait time ~ 2 weeks, study staff will begin contacting the list of potential participants. At initial contact, study recruiters will provide a detailed account of the study and its procedures, answer any questions, ascertain interest, and, if interested, schedule the baseline visit.

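### IL-6, TNF-α and CRP are compared by ANOVA on change in mean concentration, with no baseline adjustment or log scale; if the markers are right-skewed, this loses precision at about 15 completers per arm

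*Protocol*

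**What the plan says.** The Statistical Analyses paragraph (Protocol, section D) gives one method for all continuous outcomes. It opens with "we will test for differences in change in mean concentrations of muscle strength" and ends its list with "biomarkers (IL-6, TNFα, CRP) and mitochondrial health/muscle cell signaling among the groups using analyses of variance". The effect size is then fixed: "We will calculate Cohen’s d by dividing the difference in group means (control versus supplement groups) by the pooled standard deviation". The stated purpose of these comparisons is to obtain effect estimates for a larger trial.

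For associations between biomarkers and fatigue, the same paragraph leaves a choice between a parametric and a rank method: "using Pearson or Spearman’s correlations". No such choice is given for the between-arm comparison of the same markers.

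The Blood Biomarkers text says how the values arise: "Total plasma concentrations of inflammatory mediators will be determined using quantitative sandwich ELISA kits". The only covariate mentioned in the protocol is in section E, item 1 (Target Population): "age may be considered as a covariate in analyses as needed". The baseline value of the marker is not mentioned as a covariate. On size, the same item says "we aim to recruit 20 individuals per arm to participate in full study activities", expecting about 75% retention.

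**The concern.** The protocol names an outcome (change in mean concentration), a test (ANOVA) and an effect size (Cohen's d from means and a pooled SD). Two features of that choice can cost precision in a small trial.

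- **Unadjusted change.** A change score uses the baseline value with a fixed coefficient of 1. Regression on baseline estimates the coefficient and is at least as precise apart from one degree of freedom, unless the pre-post correlation is very high. The baseline measurements are collected anyway.
- **Arithmetic scale.** Concentrations cannot fall below zero. If their distribution has a long right tail, a few high values drive the mean and the SD of change, and therefore Cohen's d.

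What is at stake is the quality of the biomarker estimates and SDs passed on to the next trial. Neither feasibility nor the strength comparison is affected.

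**Working it through.** **Inputs from the protocol.** 20 per arm and about 75% retention (section E, item 1): 20 × 0.75 = 15 completers per arm. The protocol states no power, alpha, SD, correlation or distribution for the markers, so there is no figure of its own to reproduce.

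**Inputs assumed.** Two-sided alpha 0.05; log-normal marker; multiplicative treatment effect; log-scale SD 0.3 to 1.2; pre-post correlation r 0.5 to 0.8.

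**Analyses compared.**
1. Raw change, t-test (equivalent to two-group ANOVA): the plain reading of the protocol.
2. Raw follow-up adjusted for raw baseline.
3. Log change, t-test.
4. Log follow-up adjusted for log baseline.

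**Simulated power, 15 per arm, true follow-up ratio 0.6** (Monte Carlo; runs agree to about one or two percentage points):

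| log-SD | r | 1. raw change | 2. raw adjusted | 3. log change | 4. log adjusted |
|---|---|---|---|---|---|
| 0.6 | 0.5 | 41% | 63% | 62% | 72% |
| 0.8 | 0.7 | 33% | 47% | 59% | 64% |
| 1.0 | 0.7 | 19% | 28% | 42% | 46% |

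**Splitting the loss.** The gap between analyses 1 and 4 is 72 − 41 = 31, 64 − 33 = 31 and 46 − 19 = 27 points.
- Baseline adjustment alone (2 minus 1) recovers 22, 14 and 9 points.
- The log scale alone (3 minus 1) recovers 21, 26 and 23 points.

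The two shares overlap, so the split depends on the order in which the steps are taken. Baseline adjustment matters as much as the scale at log-SD 0.6; the scale matters more as skew grows. On the log scale the cost of an unadjusted change score has a closed form: variance ratio 2(1 − r)/(1 − r²) = 2/(1 + r), which is 1.33 at r 0.5 and 1.18 at r 0.7.

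**Mild skew.** At log-SD 0.3 and ratio 0.8, analysis 1 versus 4 gives 44 vs 60% (r 0.5) and 63 vs 77% (r 0.7). At log-SD 0.3, r 0.5 and ratio 0.76, analyses 1 to 4 give 58.8, 76.5, 68.3 and 79.0%, so baseline adjustment alone recovers nearly all of the gap.

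**In terms of information.** Effects were set so that analysis 4 has about 79% power. Relative efficiency is ((z_power + 1.96) for analysis 1 ÷ the same for analysis 4)². At log-SD 0.8 and r 0.7 the powers are 40.9% and 78.4%: ((−0.23 + 1.96)/(0.79 + 1.96))² = (1.73/2.75)² ≈ 0.40. The 15 per arm then work like 15 × 0.40 = 6. Over r 0.5 to 0.8 the information lost is 23-38% at log-SD 0.3, 38-49% at 0.5, 57-65% at 0.8, 68-74% at 1.0 and 76-80% at 1.2.

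**Influence of single participants.** In the median simulated trial, the two most extreme of 30 participants supply 35%, 44%, 52% and 58% of the within-arm sum of squares of raw change at log-SD 0.3, 0.6, 0.8 and 1.0. That sum of squares determines the pooled SD of change.

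**Under no effect.** Rejection for raw change is 3.2-4.9% across log-SD 0.3 to 1.2, at or below the nominal 5%. The log-adjusted analysis rejects at about 5%.

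**The case against.** The strongest case against is that this is detail for an analysis plan that is not shown. The protocol never says raw or untransformed. ANOVA on log values would fit its wording, and its phrase about concentrations also covers strength and quality of life, so it is loosely used. A reader might infer that the protocol rules out a transformation; it does not. What remains is that it does state an outcome, a test and an effect size for these markers. The plain reading is the arithmetic scale, and a more precise method is available from data already collected.

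Second, the size of the loss rests on assumptions. The documents do not show that the markers are skewed. The simulation makes the log model true by construction, and a ratio of 0.6 between two arms that both exercise has no source in the protocol. At a ratio of 0.8 and log-SDs of 0.6, 0.8 and 1.0, power is 13 vs 20%, 11 vs 17% and 7 vs 13%: low with either method. This stands, so the loss must be read as a conditional range.

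Third, a reader might blame the whole loss on skew. The split above does not support that: unadjusted change scores account for a substantial part.

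Fourth, the sample size was set on practical grounds, not power. That is true, but it does not remove the interest in precise estimates, which the paragraph gives as the aim.

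**Conclusion.** The point holds as a minor one. For IL-6, TNF-α and CRP, the stated comparison uses neither baseline adjustment nor a log scale. If the markers are right-skewed, it gives up precision that a better analysis would recover with 15 completers per arm. The information lost is roughly a quarter to just over a third under mild skew (log-SD 0.3) and more than half at log-SD 0.8 or above. This assumes a log-normal marker, a multiplicative effect and r of 0.5 to 0.8, none of which the protocol gives.

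Three stronger readings are not supported:
- **False positives.** Type I error is at or below nominal, so the planned test is not invalid.
- **Threat to the trial's conclusion.** Success is defined in section A by feasibility and the direction of the strength effect. The blood markers are described under the Secondary Outcomes heading of section D, but Aims 1 and 2 do not name them, and inflammation appears only in the text of the exploratory aim.
- **All muscle markers need logs.** The simulation does not cover them. Biopsies are optional (section E, item 8), so 15 per arm does not carry over.

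**What to change.** In the Statistical Analyses paragraph of section D, add one sentence for IL-6, TNF-α and CRP: arms are compared on log follow-up concentration adjusted for log baseline concentration, and the result is reported as a ratio of geometric means with a 95% confidence interval. State that the scale for the muscle markers will be decided measure by measure.

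The cost is that sentence. No new data, visits or participants are needed. Results for the three markers will read as ratios rather than absolute differences.
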